**Imaging variables of interest**

Our primary exposures of interest are:

- Infarct volume, measured manually through computer-assisted planimetry. Infarct volume will be measured on diffusion-weighted MRI sequences if available. If not, the last CT scan acquired prior to DOAC administration will be used.
- Presence of haemorrhagic transformation of the qualifying infarct classified by Heidelberg criteria as petechial (1a/HI1 or 1b/HI2), parenchymal (1c/PH1 or 2/PH2), or remote (3) (22).

Our secondary exposures of interest are:

- A semiquantitative classification of infarct size used previously in observational studies and in the ELAN trial (8,9,16), estimated using diffusion-weighted MRI if available, or the last eligible CT scan if not. Infarct size is classified as below:
- Minor: lesion <1.5cm maximum diameter in anterior or posterior circulation, or multiple tiny spots (“embolic shower”)
- Moderate: lesion in cortical superficial branch of anterior, middle or posterior cerebral arteries; in deep branch of middle cerebral artery; in internal borderzone territories; or two minor lesions
- Major: lesion involving complete territory of anterior, middle or posterior cerebral artery; lesion ≥ 1.5cm maximum diameter in brainstem or cerebellum; or two moderate lesions
- CT markers of cerebral small vessel disease:
- Leukoaraiosis measured through total simplified Fazekas scale (17)
- Presence of one or more lacunes according to STRIVE definition (14)
- Overall CT Small Vessel Disease score, comprising leukoaraiosis, lacunes, and atrophy (18)
- MRI markers of cerebral small vessel disease:
- Number of cerebral microbleeds on MRI, categorised as 0, 1, 2-4, and 5 or more.
- Presence of multiple cerebral microbleeds in strictly lobar distribution (suggestive of cerebral amyloid angiopathy)
- Presence of cortical superficial siderosis (focal or disseminated)
- White matter hyperintensity burden measured through total Fazekas score (19)
- Presence of one or more lacunes according to STRIVE definition
- Burden of MR-visible perivascular spaces in basal ganglia region, rated using an established five-level ordinal scale (20)
- Overall MRI Total Small Vessel Disease score, comprising leukoaraiosis, white matter hyperintensities, basal ganglia perivascular spaces and cerebral microbleeds (21)

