**Sample size estimates**

The target sample size for OPTIMAS is 3,478 participants. In an interim analysis of the first 2,965 participants, all participants had a CT, 33% had a CT after 12 hours, 24% had an MRI before DOAC commencement, and 57% had either a CT acquired between 12 hours and DOAC commencement or an MRI. Interim data suggests a primary outcome rate of 4.3% (7). Allowing a conservative 5% margin for missing or poor-quality imaging, we estimate a sample size of 1,883 participants (81 events) for analyses of infarct volume, infarct size and haemorrhagic transformation, 790 participants (34 events) for analyses of MRI markers of cerebral small vessel disease, and 3,304 participants (142 events) for analyses of CT markers of cerebral small vessel disease. Owing to the fixed sample size, formal power calculations were not appropriate.

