**Statistical analysis**

For each imaging variable of interest, we will test for modification of the effect of treatment allocation (early or delayed DOAC initiation) by including the imaging variable as an interaction term with the independent variable representing treatment allocation (based on the intention-to-treat principle) in a mixed-effects logistic regression model with the occurrence of the primary study outcome as the dependent variable. If there is a significant difference in NIHSS between the main trial groups, we will consider adjusting for stroke severity (NIHSS) at randomisation. We will adjust for clustering by including sites as random intercept terms. An interaction with p-value <0.05 will be accepted as statistically significant. We will not adjust for multiple comparisons, but significant interactions for our secondary exposures of interest will be treated as hypothesis-generating (23). We will not impute missing exposures of interest but will include in each analysis all participants for whom the relevant exposure of interest is available.

Additional secondary analyses may include:

- A sensitivity analysis excluding participants with CT imaging acquired between before 24 hours of stroke onset
- Sensitivity analyses around infarct size and volume assessed using CT only or MRI only
- Analysis of exposures of interest with respect to individual components of the primary study outcome (e.g. ischaemic stroke, ICH)
- The feasibility and reliability of automated approaches to the measurement of infarct volume

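### The MRI total small vessel disease score names white matter disease twice and leaves out lacunes; the component list should be corrected, though the number of participants affected cannot be computed from the SAP

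*SAP*

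**What the plan says.** All the relevant text is in the SAP section Imaging variables of interest, among the secondary exposures.

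- The MRI summary score is "Overall MRI Total Small Vessel Disease score, comprising leukoaraiosis, white matter hyperintensities, basal ganglia perivascular spaces and cerebral microbleeds", with citation (21).
- The CT summary score is "Overall CT Small Vessel Disease score, comprising leukoaraiosis, lacunes, and atrophy".
- White matter disease is rated once per modality. The CT list has "Leukoaraiosis measured through total simplified Fazekas scale"; the MRI list has "White matter hyperintensity burden measured through total Fazekas score". The MRI list has no separate leukoaraiosis item.
- Lacunes appear as a single marker in both the CT and the MRI list: "Presence of one or more lacunes according to STRIVE definition".

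No cut-offs or point rule are given for the MRI score. Under Statistical analysis, each imaging variable is tested as an interaction with treatment allocation at p<0.05 without multiplicity adjustment, and "significant interactions for our secondary exposures of interest will be treated as hypothesis-generating".

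**The concern.** The sentence defining the MRI score is the operative definition of a pre-specified exposure, and as a list of four components it does not work. Two of the four names refer to white matter disease, and one of those two has no MRI rating of its own. A feature that is rated on MRI, and that the SAP counts in its CT score, is absent without explanation.

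An analyst must therefore give white matter disease two points, give it one point and work with three components, or depart from the text and put lacunes in. These choices give different scores for some participants. In the first two, an interaction with the score would be reported as concerning overall small vessel disease burden although lacunes had not contributed to it.

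**Working it through.** **1. The analysis set.** Sample size estimates gives three inputs: "The target sample size for OPTIMAS is 3,478 participants", "24% had an MRI before DOAC commencement", and a 5% allowance for missing or poor imaging.

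- Participants: 3,478 × 0.24 × 0.95 = 793, against 790 stated. The 24% is rounded; 23.5% to 24.5% would give 776 to 810, so the stated figure is reproduced.
- Events at the stated 4.3% outcome rate: 790 × 0.043 = 34.0, against 34 stated.

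**2. The component lists side by side.**

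| Feature | Rated on MRI | In CT score | In MRI score as written |
|---|---|---|---|
| White matter disease | yes, once | yes | named twice |
| Lacunes | yes | yes | no |
| Basal ganglia perivascular spaces | yes | no | yes |
| Cerebral microbleeds | yes | no | yes |
| Atrophy | no | yes | no |

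**3. What a literal reading does.** Let W, L, P and M be 0/1 points for white matter disease, lacunes, perivascular spaces and microbleeds. One point per component is an assumption.

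- As written: 2W + P + M.
- With lacunes in place of leukoaraiosis: W + L + P + M.
- Difference: W − L. It is +1 with white matter disease only, −1 with lacunes only, and 0 with both or neither.

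Write w and l for the prevalences of W and L, and p11 for the proportion with both. The share mis-scored is w + l − 2·p11, where p11 = w·l + φ·√(w(1−w)·l(1−l)) and cannot exceed the smaller of w and l.

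If white matter is scored only once, the score is W + P + M. The difference is then −L, and the share mis-scored is l.

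**4. Size over assumed prevalences.** The SAP gives neither prevalence nor overlap. The ranges below assume w from 10% to 60% and l from 10% to 40%.

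| Case | Share mis-scored | Of 790 |
|---|---|---|
| Independent (φ = 0) | 18% (w = l = 0.1) to 58% (w = 0.6, l = 0.1) | 142 to 458 |
| φ = 0.3 | about 13% to 50% | about 100 to 395 |
| Fullest possible overlap, share = \|w − l\| | 0% to 50% | 0 to 395 |
| White matter scored once, share = l | 10% to 40% | 79 to 316 |

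Worked examples:

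- Low end, independent: 0.1 + 0.1 − 2 × 0.01 = 0.18.
- High end, independent: 0.6 + 0.1 − 2 × 0.06 = 0.58.
- Low end, φ = 0.3: p11 = 0.01 + 0.3 × 0.09 = 0.037, so the share is 0.2 − 0.074 = 0.126.
- High end, φ = 0.3 (w = 0.6, l = 0.1): the formula gives p11 = 0.104, above its limit of 0.1. It is held at 0.1, so the share is 0.7 − 0.2 = 0.50.

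**5. The citation.** The score cites (21). In the printed References, item 21 concerns MR signal abnormalities in dementia and normal aging, while the paper on total MRI small vessel disease burden is item 23. The other scale citations in the same list are also two behind: the CT leukoaraiosis scale cites (17), but the matching paper, on grading white matter lesions on CT and MRI, is printed as 19. That title also supports reading leukoaraiosis as white matter disease.

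**The case against.** The best case on the other side is that this is a one-word slip in describing a published score, with lacunes intended where leukoaraiosis was written. Imaging rating procedures commits the raters to validated scales where they exist. Once the consistent offset of two is noticed, the citation leads to the paper on total MRI small vessel disease burden, so the analysts may well score it correctly whatever the SAP says. This stands as a limit on the likely effect. It does not make the text right: a reader who follows the printed number reaches a different paper, and that lacunes were meant is an inference.

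A second objection is that nothing in the MRI list could supply a second white matter point, so double counting is only one reading. This also stands, which is why the single-count case is shown. Lacunes are omitted under either reading.

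A reader might infer three stronger things that the document does not support:

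- *That the score would be wrong for a large share of MRI participants.* This needs prevalences and overlap that the SAP does not give, and it needs literal implementation.
- *That the score is mostly a white matter score.* With equal weights, white matter is two of four components, so at most half.
- *That the slip is what makes the MRI and CT scores non-comparable.* The CT score includes atrophy and has neither perivascular spaces nor microbleeds, so the two differ after the correction as well. The SAP plans no comparison between them.

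Last, the exposure is one of seven MRI markers, all listed as secondary. Lacunes, white matter hyperintensities, perivascular spaces and microbleeds are each analysed separately, so no lacune data are lost.

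**Conclusion.** The definition is wrong as written: white matter disease is named twice and lacunes are left out of the MRI total score. That follows from the SAP's own lists and needs no assumption about prevalence.

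The size of the consequence is not known. The ranges in the working rest on the assumed prevalences and on one point per component, and they arise only if the text is followed rather than the published score. They show that the effect could be material or negligible; they are not an estimate for this trial.

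The reach is narrow. One secondary, hypothesis-generating exposure is affected, in an analysis set of about 790 participants and 34 events. No primary exposure, sample size or significance level changes. It is a correction worth making before the analysis, not a threat to the sub-study's main question.

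**What to change.** In the MRI total score, replace leukoaraiosis by lacunes, so that it comprises lacunes, white matter hyperintensities, basal ganglia perivascular spaces and cerebral microbleeds. Correct its citation to the paper printed as reference 23.

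The cost is one word and one reference number. All four components are already on the MRI rating list, so no new ratings are needed, and the 790 participants and 34 events are unchanged. In the same edit it would help to state the cut-off that earns each point, or to say that the cut-offs are those of the cited score.

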**Sample size estimates**

The target sample size for OPTIMAS is 3,478 participants. In an interim analysis of the first 2,965 participants, all participants had a CT, 33% had a CT after 12 hours, 24% had an MRI before DOAC commencement, and 57% had either a CT acquired between 12 hours and DOAC commencement or an MRI. Interim data suggests a primary outcome rate of 4.3% (7). Allowing a conservative 5% margin for missing or poor-quality imaging, we estimate a sample size of 1,883 participants (81 events) for analyses of infarct volume, infarct size and haemorrhagic transformation, 790 participants (34 events) for analyses of MRI markers of cerebral small vessel disease, and 3,304 participants (142 events) for analyses of CT markers of cerebral small vessel disease. Owing to the fixed sample size, formal power calculations were not appropriate.

**Statistical analysis**

For each imaging variable of interest, we will test for modification of the effect of treatment allocation (early or delayed DOAC initiation) by including the imaging variable as an interaction term with the independent variable representing treatment allocation (based on the intention-to-treat principle) in a mixed-effects logistic regression model with the occurrence of the primary study outcome as the dependent variable. If there is a significant difference in NIHSS between the main trial groups, we will consider adjusting for stroke severity (NIHSS) at randomisation. We will adjust for clustering by including sites as random intercept terms. An interaction with p-value <0.05 will be accepted as statistically significant. We will not adjust for multiple comparisons, but significant interactions for our secondary exposures of interest will be treated as hypothesis-generating (23). We will not impute missing exposures of interest but will include in each analysis all participants for whom the relevant exposure of interest is available.

Additional secondary analyses may include:

- A sensitivity analysis excluding participants with CT imaging acquired between before 24 hours of stroke onset
- Sensitivity analyses around infarct size and volume assessed using CT only or MRI only
- Analysis of exposures of interest with respect to individual components of the primary study outcome (e.g. ischaemic stroke, ICH)
- The feasibility and reliability of automated approaches to the measurement of infarct volume

**Discussion**

Based on methodological recommendations for secondary analyses of clinical trials, our imaging variables of interest are divided into primary and secondary exposures (23). Primary exposures are those for which a subgroup analysis is well-motivated by external evidence, and the results of which are intended to influence clinical practice; whereas analyses of secondary exposures are less strongly supported by external evidence and are intended to be hypothesis-generating.

We chose infarct volume measured by computer-assisted planimetry as our primary exposure of interest for CT and MRI sub-studies as the volume of infarcted tissue is thought on theoretical grounds to be a key determinant of the risk of haemorrhagic transformation, and infarct size has been associated with risk of intracranial haemorrhage and recurrent ischaemic stroke in a number of observational studies of patients initiating anticoagulation after AF-associated stroke (4). Although time-consuming, planimetry is the current gold standard for the measurement of infarct volume (24), with excellent inter-rater reliability between trained raters (25). Assessing infarct size as volume, a continuous variable, gives the greatest statistical power to detect an interaction and determine whether infarct size should influence anticoagulation timing (26). Recognising the difficulty in manually measuring infarct volume in clinical practice, we include a semiquantitative classification of infarct size as a secondary outcome for both sub-studies, and a pooled analysis with the ELAN trial, which uses this classification, is planned. In the future, improved image segmentation techniques may allow the automated measurement of infarct volume in clinical practice.

Haemorrhagic transformation is relatively common after cardioembolic stroke and often delays anticoagulation (30,31). Participants with severe parenchymal or remote haemorrhagic transformation (grade 2 or 3 by Heidelberg classification) are excluded from OPTIMAS on safety grounds. However, minor haemorrhagic transformation (Heidelberg grade 1) is not clearly associated with worse clinical outcome (32), and has not yet been shown to affect the risk-benefit balance of early anticoagulation. As haemorrhagic transformation is anticipated to be a rare baseline characteristic in the study sample, we will investigate this question by combining CT and MRI data - the Heidelberg classification has been proposed to apply to both (22). We will perform sensitivity analyses to address the possibility that the prevalence and significance of haemorrhagic transformation may vary according to imaging modality, given the very high sensitivity of blood-sensitive MRI sequences.

To our knowledge, whether neuroimaging markers of cerebral small vessel disease should influence the timing of anticoagulation initiation after ischaemic stroke is largely unstudied. It is clear that cerebral small vessel disease is the main cause of intracerebral haemorrhage overall, and likely also accounts for the majority of intracerebral haemorrhage in patients taking oral anticoagulants (27). Although haemorrhagic transformation generally occurs within infarcted brain tissue, it might be hypothesised that the risk of haemorrhagic transformation would be higher in the presence of pre-existing vascular fragility. Of the various CT and MRI markers of cerebral small vessel disease, we selected the burden of cerebral microbleeds on MRI as a primary exposure of interest as it is the most prognostically significant marker of long-term ICH risk in patients taking antithrombotics (28), and also influences the risk of ICH after intravenous thrombolysis (29).

To reflect how imaging might be used in clinical practice to decide between early and more delayed anticoagulation, we include only participants with imaging acquired before commencement of anticoagulation. We exclude imaging acquired after DOAC initiation, as this could affect some imaging features, notably the presence of haemorrhagic transformation and cerebral microbleeds. We will also consider excluding CT scans acquired fewer than 6 hours from stroke onset, as the growth of the ischaemic core and the associated development of cytotoxic oedema and CT hypodensity occurs over hours (33). We do not have an early limit on the timing of MRI, as changes on diffusion-weighted MRI appear within minutes of stroke symptom onset (34,35), although a relatively limited increase in lesion size may occur over the first 72 hours (36).

